#### Translational endpoints

Biomarkers in tissue, perfusate, bile and laboratory chemistry for outcome prediction (Early Allograft Dysfunction according to the criteria of Olthoff *et al*^14^ as well as 3-month graft survival) through NMP. This includes DNA and RNA analyses for the aforementioned purpose and future research (ie, the purpose of the analyses will be determined in the future). Samples will be stored at the central biobank (Central Biobank Charité/BIH).

### Assessments

#### Medical history

Baseline medical history will be obtained at time of inclusion to characterise the clinical status of all participants prior to transplantation. Demographic variables including age, height, weight, sex, blood group and Rhesus factor will be recorded. The indication for LT will be documented. Disease severity will be captured through the reMELD-Na score, documented together with the date of assessment. Medical history, including relevant comorbidities, will be collected.

#### Waitlist report

Comprehensive waitlist data will be collected during the 12-month intervention period to describe pretransplant organ offer dynamics and clinical prioritisation. For each recipient, the number of primary organ offers, and extended/rescue allocation offers will be documented, including offers accepted for the patient but not transplanted. All declined organs will be recorded together with the timing of the decline—before procurement, during procurement or on arrival at the transplant centre—and the documented reason. Periods during which a patient was temporarily not transplantable will be captured. These assessments provide a detailed representation of waiting time burden, offer utilisation, and centre-level decision pathways including transplant activity.

### EQ-5D-5L

Patient-reported outcomes will be assessed using the EQ-5D-5L instrument. The instrument evaluates five dimensions of health: mobility, self-care, usual activities, pain/discomfort and anxiety/depression. Each dimension is rated across five severity levels, yielding a five-digit health state profile. In addition, patients will rate their overall health status using the EQ Visual Analogue Scale (VAS), a validated 0–100 scale anchored by ‘worst imaginable’ and ‘best imaginable’ health. The EQ-5D-5L will be measured at time of inclusion, end of intervention/prior to LT, at discharge from hospital as well as 3, 6 and 12 months after LT (if applicable).

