**Methods and analysis:**

The ExTra trial is a prospective, randomised, multicentre study conducted across German transplant centres. Participants listed for liver transplantation with a reMELD-Na-Score ≤21 (refitted MELD-Natrium Score) who are not eligible for Standard or Non-Standard Exceptions will be randomised for a 1-year intervention period into two groups: the experimental arm, in which they have—in addition to regular organ allocation—the extra option to receive a graft that was initially deemed non-transplantable based on clinical criteria, but meets specified quality criteria after at least 4 hours of NMP, and the control arm, which consists of conventional allocation procedures alone. The primary endpoint is time-to-transplant, defined as the period between randomisation and transplantation. Secondary outcomes include competing events (death, disease progression or recovery without transplantation), graft and patient survival, quality of life and cost-effectiveness. Additional analyses will assess early graft function, length of hospital stay, biliary complications and 1-year post-transplant outcomes. A centralised biobank will collect perfusate, tissue and blood samples for biomarker research. Safety will be monitored through quarterly reviews by a Data Safety Monitoring Board.

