26^ while the protocol established in Groningen for the Liver Assist device consisted of 1 hour of HOPE, followed by controlled oxygenated rewarming (COR) and 2.5 hours of NMP for quality assessment.^22
25^ This protocol was also used in a modified form (90 min of COR and dual HOPE) in one study that employed both the Liver Assist and Aferetica PerLife devices.^27^

The ExTra trial will randomise patients on the waiting list to demonstrate that declined liver grafts, which meet predefined quality criteria after at least 4 hours of NMP, can be used to reduce the waiting time for LT in patients with a low MELD score who are not eligible for Standard or Non-Standard Exceptions. This is of clinical relevance given the increasing number of livers declined for transplantation in Germany, despite new technologies enabling quality assessment of these potentially transplantable organs. The utilisation rate of grafts, safety, cost-effectiveness and the effect on the waiting list practice will be evaluated as secondary endpoints. The results of this study could therefore change clinical practice in Germany and help address the medical-social dilemma of organ shortages in LT by integrating graft quality assessment through NMP into clinical practice. This could enable the acceptance of livers that are currently declined, which would certainly increase organ utilisation in Germany. To further leverage the impact of this clinical study, a translational companion study will be conducted to identify novel biomarkers for assessing and predicting graft quality in NMP.

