#### Secondary endpoints

The secondary endpoints include, among others, competing events (death, disease progression, recovery) and are also evaluated on the intention-to-treat cohort. Again, the time from randomisation until the occurrence of the event is examined. For death (corresponds to waiting list mortality) and the composite of disease progression and recovery, cause-specific Cox proportional hazards models are calculated. The same variables as for the primary endpoint are used for adjustment (reMELD-Na score and waiting time), in addition to perfusion device used (OrganOx Metra, LiverAssist or Aferetica PerLife), study centre, age and sex. Furthermore, of particular interest are the number of patients still listed for transplantation after 12 months, the overall patient survival (from randomisation to death), the quality of life (EuroQol-5 Dimension, 5-Level questionnaire - EQ-5D-5L), the graft utilisation rate (used organs/offered organs for patients on the waiting list) as well as transplantation-associated costs.

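### After inclusion, EQ-5D-5L readings are timed by transplantation rather than randomisation, which ill suits the intention-to-treat quality-of-life comparison; the named cost endpoint is also narrower than the cost-effectiveness promised

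*Protocol article*

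**What the plan says.** The EQ-5D-5L section gives an explicit list of measurement times. It opens "The EQ-5D-5L will be measured at time of inclusion, end of intervention/prior to LT, at discharge from hospital" and ends "3, 6 and 12 months after LT (if applicable"). Under Experimental arm, the ExTra option runs for 12 months from randomisation. Under Quality assessment, patients not transplanted by then return to ordinary listing and are censored. Study design and timeline and Control arm both describe structured follow-up as following transplantation.

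The Secondary endpoints section says that the secondary endpoints "are also evaluated on the intention-to-treat cohort". It counts quality of life by EQ-5D-5L among the outcomes of particular interest, "as well as transplantation-associated costs". The abstract lists "graft and patient survival, quality of life and cost-effectiveness" among the secondary outcomes, and Background and rationale says: "The utilisation rate of grafts, safety, cost-effectiveness and the effect on the waiting list practice will be evaluated as secondary endpoints".

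**The concern.** After inclusion, no EQ-5D-5L reading is set at a common time from randomisation for all patients. A transplanted patient gives the second reading on the eve of surgery. A patient still waiting gives it at about month 12. Discharge and the 3-, 6- and 12-month visits exist only for transplanted patients. When a patient is measured, and how often, is therefore decided by transplantation, which is the primary endpoint and the event the intervention should make more frequent and earlier.

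Two natural analyses would then go wrong. Comparing the arms at each post-transplant visit compares transplanted patients only, selected differently by arm. Averaging all readings by arm compares different mixes of pre- and post-transplant states. Neither is the intention-to-treat contrast that the Secondary endpoints section announces. An analysis plan can choose an interpolation rule, but it cannot recover questionnaires that were never given.

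A smaller point concerns costs. A cost-effectiveness comparison of two waiting-list strategies needs costs from randomisation in both arms, whereas the only cost item named is tied to transplantation.

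**Working it through.** **Inputs (Sample size section).** Monthly transplant hazard 0.057 (control) and 0.104 (experimental); competing-event hazard 0.0251 in both arms; 83 patients per arm; 12-month horizon.

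**Step 1: reproduce the plan's figures.** With transplant hazard λ and competing hazard κ, the proportion transplanted by month 12 is λ/(λ+κ) × [1 − exp(−12(λ+κ))].

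- Control: 0.057/0.0821 × [1 − exp(−0.9852)] = 0.694 × 0.627 = 0.435 (plan: 43.6%).
- Experimental: 0.104/0.1291 × [1 − exp(−1.5492)] = 0.806 × 0.788 = 0.634 (plan: 63.6%).

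Expected transplants are 83 × 0.435 = 36 and 83 × 0.634 = 53, matching the plan's median of 36 and 17 additional. A simulation of the Cox test at 83 per arm (20,000 runs) gave power 0.800. The planning figures stand.

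**Step 2: who has which readings.**

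| Per 83 randomised | Control | Experimental |
|---|---|---|
| Transplanted by month 12 (post-transplant visits apply) | 36 (43.5%) | 53 (63.4%) |
| Not transplanted (at most two readings) | 47 (56%) | 30 (37%) |
| of these, still waiting at month 12 | 31 | 18 |
| of these, competing event | 16 | 13 |

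**Step 3: when the second reading falls.** Among patients transplanted within 12 months, the median time t solves 1 − exp(−(λ+κ)t) = ½[1 − exp(−12(λ+κ))]. This gives t = 4.6 months (control) and 3.9 months (experimental). For those still waiting, the second reading is at month 12. For patients who leave through progression or recovery, the article does not say whether it is taken at exit or at month 12.

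**Step 4: what pooling would do.** Count six scheduled readings for a transplanted patient and two for any other, all completed. The mean number per patient is 2 + 4 × 0.435 = 3.74 (control) and 2 + 4 × 0.634 = 4.54 (experimental). Post-transplant readings make up 1.74/3.74 = 47% and 2.54/4.54 = 56% of the total. The mix differs by arm because of the primary outcome.

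**Step 5: how well interpolation copes.** The article gives no utilities, so these are assumptions: 0.70 on the waiting list, falling by 0 to 0.24 over 12 months; 0.3 or 0.5 just after transplantation; 0.60 at discharge (taken as one month), 0.75 at 3, 0.80 at 6 and 0.82 at 12 months; 0 after any competing event. Across 12 settings, the true 12-month arm difference in mean utility was 0.013 to 0.038. Linear interpolation between dated visits gave 0.016 to 0.039. The error in individual settings ran from 0.001 to 0.012, at worst about half of the true difference (0.0352 against 0.0228). It favoured the experimental arm each time. The settings covered only a flat, straight or late-accelerating decline on the waiting list; a decline steepest early on would pull the other way. Setting utility to 0 after recovery is also a simplification.

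**Step 6: beyond month 12.** Transplanted patients have readings up to 12 months after surgery. For patients not transplanted by month 12, no further reading is listed.

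**The case against.** A reader might infer that quality of life cannot be compared by randomised arm without bias at all. The documents do not support that. Every patient is scheduled for a reading at inclusion and at the end of intervention or before transplantation. Those still waiting do have a month-12 reading, and visits in transplanted patients run to 12 months after surgery, so they always reach month 12 from randomisation. Deaths can be valued at 0. A 12-month intention-to-treat contrast can therefore be approximated, and in the illustration the absolute error was small. Fewer readings in untransplanted patients is not in itself bias. The article also never mentions QALYs, and the method of analysis may properly sit in the full protocol or analysis plan. Supplemental table 1 is not shown either. All of this stands. What it does not answer is that the article's list of times is explicit, and that an analysis rule only approximates readings not taken.

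A reader might also infer that the cost comparison is loaded against the experimental arm, by 46%. That figure is only the ratio of expected transplants (52.7/36.1 = 1.46) and assumes equal cost per transplant. Extra transplants are a real cost of the strategy. The article does not define transplantation-associated costs, nor does it say that waiting-list care or failed perfusion runs are excluded. Leaving out waiting-list care would tend to disfavour the experimental arm, while leaving out perfusion of grafts then rejected would favour it. What remains is a mismatch between the endpoint named and the cost-effectiveness promised.

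**Conclusion.** The point holds as a cheap improvement to a secondary endpoint. As listed, the EQ-5D-5L schedule lets transplantation determine the timing and number of readings, and transplantation is expected in 43.5% of controls against 63.4% of the experimental arm. A visit-by-visit or pooled arm comparison would condition on that event. A 12-month intention-to-treat comparison is available only by interpolation. Its error depends on assumed utilities, and neither its size nor its direction can be read from the documents. Beyond month 12 the schedule gives nothing for untransplanted patients, and timing is unclear for those leaving through progression or recovery.

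The percentages rest on the plan's own exponential hazards. On costs, the finding is limited to inconsistent wording. The primary endpoint, its analysis and the sample size are not affected.

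**What to change.** Add the EQ-5D-5L at 6 and 12 months after randomisation for every surviving patient in both arms, whatever the transplant status and including those who have left the waiting list through progression or recovery, subject to consent. Base the intention-to-treat quality-of-life comparison on these readings and state how deaths enter it. Keep the transplant-anchored visits to describe recovery after surgery.

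The cost is at most two short questionnaires per patient, given at routine reMELD-Na contacts or by post. For patients still waiting at month 12, the end-of-intervention reading already serves as the second. The downside is minor patient burden and some data entry. Recruitment is planned to run to 31 May 2028, so many patients can still be covered. Those who passed month 6 or 12 before the amendment would rely on interpolation.

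For costs, bring the Secondary endpoints wording into line with the abstract and rationale: count costs from randomisation in both arms, including hospital care while waiting and perfusion runs on grafts then rejected. This needs hospital billing data for the waiting period.

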#### Bloodwork

Blood sampling will be performed according to routine clinical practice, avoiding additional venipuncture whenever possible. Timepoints are at time of inclusion, end of intervention/prior to LT, postoperative days 1 to 7 and day 10, at discharge from hospital as well as 3, 6 and 12 months after LT (if applicable). Laboratory analyses have been minimised to reduce participant burden while maintaining the parameters necessary for evaluating perioperative risk and early graft function. The panel includes complete blood count, sodium, liver enzymes (Aspartate Aminotransferase (AST), Alanine Aminotransferase, Gamma-Glutamyl Transferase, Alkaline Phosphatase), bilirubin, International Normalized Ratio, creatinine and urea.

#### Donor information

Detailed donor characteristics will be recorded to support evaluation of graft quality and donor-derived risk factors. Donor demographics, blood group, Rhesus factor, viral serologies (HCV antigen, HBc antibody, HIV antigen) and whether the graft was split will be documented. The location of donation and cause of death will be included. Donor management data, including vasopressor requirements and a complete biochemical profile, will be collected. Cold ischaemia time will be calculated from the initiation of cold perfusion in the donor to the time the graft is removed from ice at the transplant centre or when normothermic perfusion begins.

#### Preoperative status

The clinical condition immediately prior to transplantation will be documented, including the reMELD-Na score, the need for dialysis or mechanical ventilation and the administration of norepinephrine or other catecholamines. Time spent on the waiting list will be recorded in days.

#### Postoperative status

The early postoperative course will be evaluated through documentation of organ support requirements and transfusion needs. Data collected include the requirement for dialysis, mechanical ventilation, vasopressor therapy and the intraoperative administration of red blood cell concentrates, fresh frozen plasma, platelet concentrates, PPSB, tranexamic acid and fibrinogen. This stretches throughout the inpatient hospital stay of the LT and will be documented once in the eCRF at discharge.

#### Scores

##### Early Allograft Failure Simplified Estimation score

The Early Allograft Failure Simplified Estimation score will be determined on postoperative day 10 to quantify the risk of early allograft failure. The score integrates pretransplant disease severity, perioperative transfusion requirements, the occurrence of early postoperative thrombosis and the temporal evolution of AST, platelet count and bilirubin across the first 10 postoperative days. Centre transplant volume is incorporated as an additional parameter. The resulting composite metric offers a robust prediction of early graft failure.^28^

##### Balance of Risk Score

The Balance of Risk (BAR) score will be calculated prior to transplantation to estimate the risk of early graft failure. It incorporates the MELD score at transplant (excluding exception points), the need for retransplantation, pretransplant life support status, recipient age, cold ischaemia time and donor age. The BAR score supports risk stratification and provides prognostic context for early post-transplant outcomes.^15^

##### Comprehensive Complication Index

The Comprehensive Complication Index (CCI) will be used to quantify postoperative morbidity by integrating all postoperative complications into a single continuous score ranging from 0 (no complications) to 100 (death). Derived from the Clavien-Dindo classification but offering greater sensitivity and granularity, the CCI enables a comprehensive assessment of postoperative burden.^29
30^ The CCI will be calculated at hospital discharge and at postoperative day 90 to capture both early and later complications.

### Follow-up information

Follow-up evaluations will document all postoperative complications together with their diagnostic and therapeutic management. Additional clinical events—including rejection episodes, readmissions, retransplantation, relisting and death—will be recorded with corresponding dates and explanatory notes. Biliary complications will be documented in detail.

### MRCP

A routine Magnetic Resonance Cholangiopancreatography (MRCP) will be performed 12 months after transplantation to assess biliary anatomy and detect biliary complications. Examinations will be conducted at 1.5 T or 3 T using standardised sequences, including axial and coronal T2-weighted imaging, two-dimensional and three-dimensional MRCP, diffusion-weighted imaging and T1 in-phase/out-of-phase imaging. Gadolinium-based contrast administration is optional but recommended for vascular assessment, and hepatobiliary contrast agents may be used when clinically indicated. All costs for MRCP examinations are covered in the trial.

### Biobank sampling

Participants will have the option to opt in for the biobank at the time of informed consent. Biobank procedures will be implemented uniformly across participating centres in collaboration with the Central Biobank Charité/BIH, which provides standardised collection kits, aliquoting materials and detailed processing instructions. Blood samples will be obtained at defined perioperative time points—before transplantation, 1 hour after reperfusion and on postoperative days 1 and 3—using routine clinical blood draws when possible (online supplemental table 2). These samples will include 10 mL of serum, 10 mL of EDTA whole blood, and one PAXgene blood sample. Since blood sampling is a routine part of preoperative care and postoperative follow-up, only additional material necessary for the study will be obtained. Liver wedge biopsies will be collected before machine perfusion or after organ preparation, after completion of NMP in the ExTra arm and 1 hour after reperfusion. Perfusate samples will be collected at defined time points, including before the start of perfusion, 15 min after initiation, at hourly intervals during the procedure and at the conclusion of NMP in the ExTra LT study arm, with 1.5 mL per sample. Additionally, bile samples will be collected every 2 hours during perfusion and at the end of NMP in the same study arm, with 500µl per sample. All samples will be processed locally (figure 2), frozen and transferred to the central biobank on dry ice, with transport costs covered by the project.

**Figure 2 F2:**
[figure not shown]
Biobank sample collection, preparation and storage in the ExTra trial. LN2, liquid nitrogen; RT, room temperature.

### Sample size

The primary statistical objective is to show that the cause-specific HR for the transplant risk between the two randomised groups is not equal to 1. The assumptions for the data-generating process are based on data from Eurotransplant in 2022: Within 12 months, 43.6% of patients with a MELD ≤25 (corresponds to reMELD-Na ≤21) who were not eligible for Standard or Non-Standard Exception were transplanted, 19.1% had a competing event (death, progression or recovery) and 37.2% remained on the waiting list and were censored in this study.

As a treatment effect, an increase in the transplantation rate of 20% to 63.6% was assumed, while the risk of the competing event remains unchanged. A 20% increase in the transplantation rate through the ExTra option is realistic, as 385 LTs were performed in Germany in 2022 in patients with MELD ≤25 without standard/non-standard exception MELD criteria, while 133 of 217 declined grafts would have been potentially acceptable after a quality assessment using NMP, representing approximately 20% additional grafts in the study population based on an estimated 50% acceptance rate following NMP.

Assuming exponential distributions for time to transplant and time to competing event, the data were simulated to fit this pattern. The parameter of the exponential distribution for time to transplant (in months) was 0.057 for the control group and 0.104 for the intervention group. The parameter for the competing risk was 0.0251 for both groups. A Cox proportional hazards model was used to estimate the transplant HR between the ExTra LT group and the control group.

Based on 1 000 000 simulations, a sample size of N=83 per group was calculated for a two-sided type I error of 0.05 and a power of 0.8. Considering a dropout rate of 10%, a total of 93 patients will be recruited per group. A median of 36 transplantations is expected in the control arm. It is expected that 4–29 additional transplantations (median: 17) will be performed in the experimental arm.

This number of cases can probably be reached with a recruitment period of 36 months. A 12-month intervention phase is planned, followed by a 12-month follow-up phase. The study will thus end when all 83 patients in each treatment group have completed the 12-month follow-up after randomisation/transplantation.

